## Abstract

**Background:**

Low-dose computed tomography (LDCT) screening is promising for the early detection of lung cancer (LC) and the reduction of LC-related mortality. Despite the implementation of LC screening programs worldwide, recruitment is challenging. While recruitment for LC screening is based on physician referrals and mass advertising, novel recruitment strategies are needed to improve the enrollment of high-risk individuals into LC screening.

**Objective:**

We aim to identify whether patients with LC can act as advocates to enroll their family members and close contacts into LC screening and whether this strategy increases screening uptake at the population level.

**Methods:**

We designed a prospective cohort study comprising 2 cohorts constituted between June 2023 and January 2024 with a prospective follow-up of 18 months. Patients with LC (cohort 1) are approached at clinics of the McGill University Health Centre, educated on tools for communicating with family members and close contacts about the benefits of LC screening, and invited to refer their close ones. Referred individuals (cohort 2) are directed to this study’s web-based questionnaire to assess their LC risk score with the PLCOm2012 (Prostate, Lung, Colorectal and Ovarian Cancer Screening Trial) prediction model. Individuals meeting the eligibility criteria for LC screening (PLCOm2012 score ≥2% and aged 55-74 years) are directed toward the Quebec LC screening program. Data collected include sociodemographic characteristics, health literacy and smoking status (all participants), patient activation (cohort 1), perceived risk of LC, and generalized anxiety at baseline and at 28 days (cohort 2). LDCT completion within 18 months from referral is assessed from health records. Focus groups will identify the barriers and facilitators in the uptake of LC screening and preventative behaviors based on perceived genetic and clinical LC risks. The primary outcomes are the number of referred participants per survivor of LC and the mean risk of LC of the referred population based on PLCOm2012 scores. The secondary outcomes are the proportion of (1) participants eligible for LC screening; (2) participants eligible for screening who complete LDCT screening within 18 months of referral from a survivor of LC; (3) participants showing interest in genetic testing to inform LC risk; and (4) participants showing interest in a smoking cessation program. Multivariable logistic regression will identify the predictive factors of being referred for LC screening. PLCOm2012 scores will be compared for referred participants and controls from the provincial LC screening program.

**Results:**

Overall, 25 survivors of LC and 84 close contacts were enrolled from June 2023 to January 2024, with followed up through July 2025. The results are expected by the end of 2025.

**Conclusions:**

We describe an approach to LC screening referral, leveraging patients with LC as advocates to increase screening awareness and uptake among their family and peers.

**Trial Registration:**

ClinicalTrials.gov NCT05645731; https://clinicaltrials.gov/ct2/show/NCT05645731

**International Registered Report Identifier (IRRID):**

DERR1-10.2196/58529

## Introduction

### Background

Almost three-quarters of lung cancers (LCs) are diagnosed at stages III and IV with poor overall survival [1,2]. LC remains the cancer with the highest mortality rate, with high rates of comorbidities also [3,4]. The projected increase of LC burden in Canada calls for improving its early detection and preventative strategies [5]. Low-dose computed tomography (LDCT) screening of high-risk individuals is promising for early detection and reduction of LC-related mortality [6]. With more than 50,000 high-risk individuals enrolled, the pioneering National Lung Screening Trial has shown a 20% reduction in LC-related mortality with LDCT screening compared to standard chest radiography [7]. Evidence supporting this screening strategy was further supported by the NELSON (Nederlands-Leuvens Longkanker Screenings Onderzoek Trial), Pan-Canadian Early Detection of Lung Cancer Study, and UK Lung Cancer Screening Trial [8,9], leading to recommendations for screening high-risk individuals and the implementation of LC screening programs in North America and Europe [10].

The efficiency of LC screening programs relies on the optimization of the risk-benefit ratio and ensuring high participation rates within individuals with a higher risk of LC. Efforts to improve screening uptake within these groups are necessary as the preliminary uptake rates from pilot programs in the United States, Canada, and Europe were suboptimal, with only 4% to 13% of eligible individuals enrolling in LC screening [11,12]. Recent scoping reviews identified the barriers to LC screening uptake, with the most important barriers being the lack of awareness of screening programs, perceived smoking-related stigma, socioeconomic difficulties, and fear of receiving a cancer diagnosis. Furthermore, individuals facing these barriers have concomitantly higher risk of LC [13,14]. For example, in Canada, the highest rates of LC are clustered among individuals living in rural areas with lower socioeconomic status, who also have lower access to screening programs for those geographical and socioeconomic reasons [15,16]. Strategies to reach those most socially disadvantaged groups are thus imperative to guarantee the efficiency of LC screening.

Survivors of LC are empowered with valuable knowledge on their disease’s trajectory, from diagnosis to treatment. By sharing their stories within their communities, they can empower other individuals in similar health states. Due to a combination of both genetic and shared risk factors such as smoking or exposure to radon, individuals with a first-degree relative with a history of LC have a 2- to 3-fold higher risk of LC compared to the general population [17]. In a qualitative study, among individuals eligible for LDCT screening per the US Preventative Services Task Force, Roth et al [18] demonstrated that having friends or family members being treated for LC was a major motivator for being screened themselves.

So far, no previous studies have examined the impact of using survivors of LC as sources of education and referral for peers and family members who may be eligible for screening. We hypothesize that survivors of LC would be willing to refer family members or peers to LC screening, leading to a positive impact on the uptake of both the preventative and screening behaviors of the referred population. This study thus aims to determine the feasibility and acceptability of referral to LC screening through patients with LC referring their close ones to LC screening and to assess the early impact of this novel recruitment strategy on the uptake of LC screening and the patients’ outcomes.

### Objectives

We aim (1) to examine if patients with LC are willing to refer family members or close contacts to LC screening and if referral is associated with increased patient activation; (2) to examine if targeted enrollment of family members or close contacts of patients with LC for LC screening leads to increased engagement of individuals at higher risk of LC compared to referral through usual care; and (3) to examine the barriers and facilitators on the uptake of preventative strategies and LC screening, based on perceived genetic and clinical LC risks.

## Methods

### Study Design

This is a prospective cohort study of 2 separate cohorts.

### Participants Eligibility and Recruitment

#### Cohort 1

The first cohort includes biopsy-proven patients with LC aged older than 18 years at various stages in their disease trajectory, including those undergoing clinical surveillance. Participants in cohort 1 are recruited into this study either through discussion with trained research staff approaching them in the clinical settings or through posters or pamphlets available for viewing in the waiting areas of the clinics. The clinical settings where participants are recruited include the thoracic surgery clinic, pulmonary oncology clinic, pulmonary procedural suites, and chemotherapy infusion centers located at the McGill University Health Centre, one of the largest university hospitals in Montreal, Canada. Recruitment discussions and materials invite these patients to access this study’s website [19]. The web page section directed at participants in cohort 1 (Figure 1A) includes educational material on the rationale for LC screening and the methods on how to approach and discuss LC screening with peers and family members.

**Figure 1 figure1:**
[figure not shown]
Screenshot of the web page for survivors of lung cancer and their close contacts. LC: lung cancer.

Patients interested can consent and enroll through this study’s website using digital or paper forms. Participants are invited to provide contact information (email or phone number) for the close ones they wish to refer for inclusion in the second cohort of our study. They are also advised to inform their close contacts that they shared their details with the research team and that their informed consent will be mandatory before participation.

#### Cohort 2

The second cohort includes participants being referred for inclusion into our study by the participants of cohort 1. Referred participants should be aged older than 18 years. Individuals with a personal history of LC are excluded. Referred participants are contacted by our research team through emails, phone calls, or through a recruitment pamphlet mailed for those without internet access. Participants are encouraged to access our study’s website [19]. The web page section directed at cohort 2 (Figure 1B) provides general information on LC, its epidemiology, information on LC screening programs and the risk-based eligibility, and information on risk mitigation strategies such as smoking cessation and home radon testing. The enrollment of referred participants is also carried out with a submittable digital form available on this study’s website. Participants lacking the digital literacy to enroll by themselves are contacted by the research team to enroll over the phone or through mailed material.

Once enrolled, participants have their 6-year risk of LC estimated with the PLCOm2012 (Prostate, Lung, Colorectal and Ovarian Cancer Screening Trial) risk model [20]. The risk prediction PLCOm2012 model has been extensively validated in previous studies [21,22]. The PLCOm2012 model has also shown adequate properties to discriminate patients with LC in a large cohort of Quebec smokers [23]. Moreover, data from the International Lung Screening Trial have shown that the PLCOm2012 model was more efficient compared to the US Preventative Services Task Force 2013 criteria to identify high-risk individuals to enroll into LC screening programs [24]. Participants who meet the eligibility criteria for the provincial LC screening program (ie, aged between 55 and 74 years and PLCOm2012 score ≥2%) are directed toward the provincial LC screening program to complete LDCT.

### Website and Educational Material

This study’s website [19] and educational material were developed based on 3 main pillars: accessibility, comprehensibility, and inclusivity. First, we succinctly presented information to account for the health literacy level of the targeted population. Individuals at high risk of LC and with lower education levels are significantly less likely to enroll for LC screening and engage in harm-reduction programs [25], underlining the importance of presenting information comprehensible for all. This study’s website content was developed in collaboration with current patients with LC with written material created to be comprehensible at a 5th-grade reading level and above. Second, audiovisual contents are more easily comprehensible and with lower decisional conflict when used as a patient decision aid compared to information presented in textual format [26]. The audiovisual format is also more inclusive of participants with very low literacy. In collaboration with the digital media company Tactica Interactive [27], videos were produced to include the textual information of the website in audiovisual format. Lastly, for participants interested in enrolling in this study but lacking the digital literacy to enroll by themselves, information is provided on this study’s website to contact this study’s research staff (email address and telephone number).

### Outcomes

The primary and secondary outcomes are summarized in Table 1.

**Table 1 table1:** Study outcomes.

Outcomes			Methods
**Primary outcomes**			
	Number of referred participants per individuals with LC^a^ (survivors of LC)	Questionnaire: cohort 1	
	Mean risk of LC in the referred population	Questionnaire: cohort 2 PLCOm2012 model	

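### The second primary outcome averages PLCOm2012 over all referred adults, so alone it measures objective 2 weakly, and the article leaves unsettled whose mean is compared with the program

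*Protocol article*

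**What the plan says.** **The outcome.** Table 1 lists "Mean risk of LC in the referred population" as a primary outcome. The abstract has the same definition: "the mean risk of LC of the referred population based on PLCOm2012 scores". Neither limits it by age or smoking.

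**Who can be in cohort 2.** The Cohort 2 section under Participants Eligibility and Recruitment says "Referred participants should be aged older than 18 years" and "Individuals with a personal history of LC are excluded". It gives no smoking criterion and no upper age limit. On scoring it says "Once enrolled, participants have their 6-year risk of LC estimated with the PLCOm2012" model, with no subgroup left out.

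**Support for the score.** The same section states "The risk prediction PLCOm2012 model has been extensively validated in previous studies", without naming a population. It then credits the model with "adequate properties to discriminate patients with LC in a large cohort of Quebec smokers". A third citation concerns selecting high-risk individuals for screening. Ages 55-74 with a score of at least 2% are given as the provincial program's eligibility rule.

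**What the outcome serves.** The second objective asks whether enrolling survivors' contacts "leads to increased engagement of individuals at higher risk of LC compared to referral through usual care".

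**The comparison.** Quantitative Analysis defines cases as referred participants eligible for screening, with 1:1 age-matched controls from people referred, or self-referred, to the program. The next sentence describes the t test on mean scores as one of cohort 2 participants against those controls, without the eligibility condition.

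**The concern.** Objective 2 is about engaging people at higher risk. A mean over everyone referred answers a different question. It depends on the mix of contacts as well as on how many high-risk people were reached. A survivor who brings in one high-risk sibling and two low-risk relatives lowers the mean compared with one who brings in the sibling alone, yet both have engaged one high-risk person. The first primary outcome counts referrals, so extra low-risk referrals push it up while they push the second down.

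The article restricts the denominator of other outcomes in Table 1: the smoking cessation outcome covers current smokers only, and the LDCT outcome covers eligible people only. It evidently expects non-smokers and ineligible people in the cohort, but sets no such restriction on the mean.

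If the comparison population is not fixed before analysis, two different means can each be presented as the planned one, and they may lead to different conclusions about objective 2.

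**Working it through.** **1. The plan's own figure.** The Sample Size section gives 194 referred participants for 80% power at α .05, a 20% difference and a 40% baseline. Reading this as 40% against 60%, two-sided:

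n per group = [1.960·√(2·0.5·0.5) + 0.842·√(0.4·0.6 + 0.6·0.4)]² / 0.20² = (1.386 + 0.583)² / 0.04 ≈ 96.9, so 97 per group and 194 in total.

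The figure is reproduced, but it concerns proportions. The article gives no expected mean or SD for PLCOm2012 and no age or smoking mix, so the effect on the mean can only be illustrated.

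**2. How the all-referred mean responds to mix.** Let f be the share of high-risk contacts, mH their mean score and mL that of the others: overall mean = f·mH + (1 − f)·mL.

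Assumed values: 20 high-risk contacts all at 4%, and a varying number of low-risk contacts all at 0.3%. The last row totals 84, the number of contacts enrolled. The last two columns divide by the 25 survivors.

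| Low-risk contacts added | All-referred mean | Share scoring ≥2% | Referrals per survivor | Scoring ≥2% per survivor |
|---|---|---|---|---|
| 0 | 80/20 = 4.00% | 20/20 = 100% | 20/25 = 0.80 | 0.80 |
| 10 | 83/30 = 2.77% | 20/30 = 67% | 30/25 = 1.20 | 0.80 |
| 20 | 86/40 = 2.15% | 20/40 = 50% | 40/25 = 1.60 | 0.80 |
| 40 | 92/60 = 1.53% | 20/60 = 33% | 60/25 = 2.40 | 0.80 |
| 64 | 99.2/84 = 1.18% | 20/84 = 24% | 84/25 = 3.36 | 0.80 |

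Only the last column is unaffected by the low-risk contacts.

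**3. Sensitivity to the assumptions.** With f = 0.4, mH from 3% to 6% and mL from 0.1% to 0.8%:

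- lowest: 0.4·3 + 0.6·0.1 = 1.26%
- highest: 0.4·6 + 0.6·0.8 = 2.88%

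The direction does not depend on these choices, but the size does.

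**4. The two readings of the comparison.**

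- *All of cohort 2* (Table 1, and the wording of the t test): the mix effect above enters in full. Age matching also becomes awkward, since a program for ages 55-74 is unlikely to supply a control for a young adult.
- *Eligible participants only* (the definition of cases): every case scores at least 2% by definition, so in the table above the case mean stays at 4.00% in every row. This mean cannot show whether referral reached high-risk people, because reaching the threshold is the entry condition. The article does not say that controls must also be eligible, and Sample Size puts eligibility among program referrals at 40%. If controls are not restricted, only one side has a floor of 2%.

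Neither reading gives a clean comparison for objective 2, and the article does not say which applies.

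**The case against.** The strongest reply is that composition is a result, not noise. Survivors are taught about screening and choose whom to refer, and friends count as well as family. A low mean would show that the strategy brings in low-risk people, which matters in a pilot of feasibility and early impact. The mean is also not read alone, since referrals per survivor and the proportion eligible stand beside it and together give eligible contacts per survivor. Usual-care referrals are mixed too, with 40% eligible. Restricting the mean after enrollment has closed would redefine a primary outcome and discard part of a sample of 84.

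Most of this stands, and it argues for keeping the all-referred mean as a description of targeting. It does not make that mean a good measure of how many high-risk people were engaged, and it does not settle which population is compared with the program.

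A reader might also infer four stronger points that the article does not support:

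- *The score is used outside its valid age range.* Ages 55-74 are stated only as the program's eligibility band, not as the model's range.
- *No support is cited for the score.* General validation is cited with its population unstated, and what those sources cover cannot be checked here.
- *The mean reflects only who is in the family.* Survivors select whom to refer, so the mean mixes reach with composition. The Limitations section does expect first-degree relatives to be over-represented.
- *Never-smokers vanish from the calculation.* The article does not say how they are handled, and that detail may stand in a fuller document.

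**Conclusion.** The concern holds in a limited form. As defined, the second primary outcome covers all referred adults, and no cited support is stated to cover the never-smokers and young adults it may include. Alone it is a weak measure of objective 2, because it falls when low-risk contacts are added and the number of high-risk people reached is unchanged. On assumed scores of 4% and 0.3% the fall is from 4.00% to 1.18%. The actual size is unknown, because the enrolled contacts' age and smoking mix is not reported.

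The population for the comparison with the program is unsettled between Table 1 and Quantitative Analysis. This rests on the article's wording and needs no numerical assumption. It has not been shown that the outcome will give a wrong answer in this study. Setting a group mean against the 2% cut-off would also be uninformative, since that threshold applies to individuals.

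**What to change.** Record the following in a dated document before analysis:

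1. Reconcile Table 1 with Quantitative Analysis, stating which population the descriptive mean covers and which one enters the comparison.
2. Keep the all-referred mean as a description of targeting. State how never-smokers are handled in it and how many there are.
3. Base the comparison with the program on referred ever-smokers aged 55-74, not selected on score, with the same restriction applied to program referrals.
4. Report the number of referred people scoring 2% or more per survivor.

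Cohort 2 needs no new data, since age and smoking history are already collected. For program referrals, the restriction assumes that age and smoking history can be obtained along with their scores. The downside is that fewer of the 84 contacts enter the comparison, so its confidence interval is wider. Because enrollment ended in January 2024, the change should be labeled openly as a clarification made after enrollment, with the all-referred mean still reported.

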**Secondary outcomes**			
	Proportion of participants eligible for the Quebec provincial LC screening program	Questionnaire: cohort 2 PLCOm2012 model	
	Proportion of participants eligible for screening who complete LDCT^b^ screening within 18 months from referral	Provincial health data	
	Proportion of participants who demonstrate interest in undergoing genetic testing to inform their LC risk	Questionnaire: cohort 2	
	Proportion of individuals who demonstrate interest in a smoking cessation program among referred participants who are current smokers	Questionnaire: cohort 2	
	Barriers and facilitators in the uptake of LC screening and preventative strategies, based on perceived LC risk	Focus groups: cohort 1 and cohort 2	
	Number of visitors on the study’s website for referred participants	Google analytics data	

^a^LC: lung cancer.

^b^LDCT: low-dose chest tomography.

### Data Collection

#### Overview

Data are collected using the REDCap (Research Electronic Data Capture; Vanderbilt University) platform [28]. Participants are sent links to complete the web-based questionnaires.

Baseline data collected for all participants include sociodemographic characteristics (age, sex, education level, and ethnicity), health literacy, and smoking status. Health literacy is assessed with the 3-item Brief Health Literacy Screen [29] questions: “How often do you have someone help you read hospital materials?” “How confident are you filling out medical forms by yourself?” and “How often do you have problems learning about your condition because of difficulty understanding written information?” rated on 5-point Likert scales.

#### Cohort 1

For participants with LC (cohort 1), the phase of LC trajectory (investigative, treatment, or surveillance), tumor stage, performance status (as defined per Eastern Cooperative Oncology Group performance status grading), and their relationship to the referred participants are collected. The degree of self-empowerment they experienced by referring peers and family members for LC screening is assessed using the 13-item Patient Activation Measure (PAM) questionnaire [30]. The 13-item PAM questionnaire is a validated instrument to measure patient knowledge, skills, beliefs, and confidence for self-managing health. Patient activation stands as an important pillar of patient-centered care [31], and evidence has shown that being engaged and active in one’s own care is linked to better outcomes [32]. For each participant with LC, the number of unique web page visits is quantified using Google Analytics, and the number of referrals per participant with LC is collected. For participants who refer family members only, supplementary questions are asked to explore the potential barriers: “I don’t feel comfortable speaking with friends or close contacts about their health”; “I did not want my friends or close contact who smoke or used to smoke feel judged about their smoking”; “I did not want my friends to worry about their risk of LC”; “Speaking about LC screening and/or LC in general brings up negative emotions for me”; “I don’t see or speak with my friends or close contacts very often”; and “This study did not help me feel more comfortable discussing the potential benefits of LC screening.”

#### Cohort 2

For referred participants (cohort 2), the web-based questionnaire collects their known personal history of chronic obstructive pulmonary disease, prior exposure to radon or asbestos, smoking habits, and nicotine dependence using the Fagerström Tolerance questionnaire [33]. Data are used to calculate their PLCOm2012 six-year LC risk. The perceived risk of developing LC is assessed by asking “Compared with others your age, what do you think your chances are of being diagnosed with LC during your lifetime?” rated on a 5-point Likert scale. We also assess whether referred participants believe their risk is high or low due to genetics or smoking exposure and which they think is more important in increasing their lifetime LC risk. Generalized anxiety is assessed at baseline using the General Anxiety Disorder 7-item questionnaire (GAD-7) [34], and a question asks if they believe their anxiety is associated with their perceived risk of LC. We repeat the GAD-7 at 28 days after enrollment to assess the impact of the LC screening risk assessment on anxiety levels. Patients will be asked to give their consent to access their provincial health records within the 18 months following their enrollment in this study. Extracted data will consist of whether these participants underwent LC screening via LDCT within 18 months after enrollment. No data about the results of the LDCT imaging will be extracted.

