### Statistical Analysis

#### Quantitative Analysis

Participants with LC who refer at least one peer for participation will be compared to those who did not refer a peer for participation. To identify the predictive factors of referral, multivariable logistic regression will be used, adjusting for age, sex, educational attainment, health literacy, PAM score, and phase of LC trajectory. The dependent variable in the logistic regression will be referral by patients with LC. Using logistic regression, we will also examine if increased patient with LC activation is associated with increased odds of referral. Chi-square tests and 2-tailed *t* tests will be used for comparisons of categorical and continuous variables.

Referred participants who are eligible for LC screening will be considered as cases. A control group will be selected from patients who were either self-referred or referred by their primary care physician to the Quebec LC screening program and matched by age (1:1). To determine if participants in cohort 2 have a higher risk of LC than the controls, the mean PLCOm2012 scores will be compared using 2-tailed *t* tests in our cohort and in the Quebec LC screening program. The predictive factors of being eligible for LC screening and whether being referred by survivors of LC is associated with increased odds of being eligible will be examined using multivariable logistic regression. We will account for clustering among individuals referred by the same family member using a random effect model.

Spearman coefficients will be calculated to assess the correlations between the actual risk and the perceived risk of LC. Kruskal-Wallis tests will be used to compare actual and perceived risks of LC with different levels of anxiety. Odds ratios and their 95% CIs will be reported. All statistical analyses will be conducted using R (version 4.2.0; R Foundation for Statistical Computing).

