## Discussion

### Principal Findings

This paper describes the protocol of a pilot study examining the acceptability, feasibility, and impact of an innovative strategy of referral using patients with LC as advocates to increase the uptake of LC screening among individuals with high risks of LC. Increasing the uptake of LC screening for high-risk individuals is crucial as early detection of LC with LDCT has proved effective in reducing LC-related mortality by 20% and all-cause mortality by 7% [9]. LC screening with LDCT presents unique barriers that hamper the implementation and efficiency of these programs at the population level. In our study, survivors of LC receive education aimed at increasing awareness and enrollment in LC screening programs. We postulate that encouraging survivors of LC to empower and refer their close ones can not only have a positive effect on uptake rates for LC screening but can also improve patient activation and the psychosocial and clinical outcomes of patients with LC themselves.

LC is clustered among individuals with lower socioeconomic status who often also reside in rural areas [15,16,35,36]. The low screening uptake within these subpopulations has been well-established through prior LC screening programs [37]. Determining eligibility for screening is unique to LC screening and requires more extensive shared decision-making discussions between provider and patient compared to other cancer screening programs. As a result, primary care physicians need to dedicate a significant portion of a clinical visit to an LC screening discussion, which can be time-consuming. These subpopulations often face limited access to health care services while concomitantly having a high burden of clinical comorbidities. Thus, health care visits are both limited in frequency and in time as the other comorbidities may require further investigation. A recent study has shown that 67% of primary care physicians would not engage in LC screening discussions if they expected that the discussion would exceed 8 minutes [38]. Placing the referral burden entirely on primary care physicians appears to be unrealistic. These subpopulations with a higher risk of LC may benefit from this approach of encouraging survivors of LC to raise awareness within their social networks and reduce the burden placed on the providers servicing these groups.

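### Patient activation is described as a result of referring but modelled as a predictor of referring, and the plan does not say when it is measured

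*Protocol article*

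**What the plan says.** Three places in the protocol article put referral first and activation second.

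- Objectives: the second half of the first aim asks "if referral is associated with increased patient activation".
- Data Collection, Cohort 1: "The degree of self-empowerment they experienced by referring peers and family members for LC screening is assessed using the 13-item Patient Activation Measure".
- Discussion, Principal Findings: the authors postulate that having survivors refer their close ones may raise screening uptake, "but can also improve patient activation and the psychosocial and clinical outcomes of patients with LC themselves".

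Statistical Analysis, Quantitative Analysis, runs the other way. It states "The dependent variable in the logistic regression will be referral by patients with LC". The covariates of that model are given as "adjusting for age, sex, educational attainment, health literacy, PAM score, and phase of LC trajectory". The one analysis that names activation is "we will also examine if increased patient with LC activation is associated with increased odds of referral".

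The article does not say when the PAM is given or how often. For the anxiety scale in cohort 2 it does: "We repeat the GAD-7 at 28 days after enrollment". Table 1 lists activation neither as a primary nor as a secondary outcome.

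**The concern.** One score cannot be defined as what referring produces and also serve, without comment, as an explanation of who refers. If the score is taken after referral, a positive coefficient is compatible with activated patients referring more, with referring raising activation, or with both, and the planned model cannot separate them. The same score is in the adjustment set, so the coefficients for education, health literacy and disease phase may be distorted too.

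What is at stake is the interpretation of the activation half of the first objective and of the model for predictors of referral. Willingness to refer, the two primary outcomes and the analyses of cohort 2 are not affected.

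**Working it through.** **Is there a figure to reproduce?** No. The only calculation in the article, under Sample Size, concerns the referred contacts and has no bearing on the PAM. The check is therefore of the text, with an illustration under assumed effects.

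**1. The two possible timings**

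| | PAM taken after referral | PAM taken before referral |
|---|---|---|
| Description in Data Collection | Fits | Wrong: nothing has yet been experienced by referring |
| PAM as predictor and covariate in Quantitative Analysis | Conditions on a possible consequence of the outcome | Sound on this point |
| Can that score show that referring raises activation? | Only as a cross-sectional difference, unless a pre-referral score also exists | No |

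The sections conflict under either timing. A second sign of the conflict is that empowerment gained by referring has no meaning for patients who refer nobody, yet they are the comparison group in Quantitative Analysis.

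**2. Size of the PAM odds ratio if the PAM follows referral**

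Assume that prior activation has no effect on referral, that PAM is normal with the same SD in both groups, and that referring raises it by d SD. The log odds of being a referrer is then linear in PAM with slope d per SD, so OR = exp(d).

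- d = 0.3: exp(0.3) = 1.35
- d = 0.5: exp(0.5) = 1.65
- d = 0.8: exp(0.8) = 2.23

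A simulation with 400,000 patients per scenario gave 1.64 at d = 0.5 and 2.24 at d = 0.8. With a pre-referral PAM it gave about 1.00.

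**3. Effect on another coefficient**

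Assume that health literacy has a true OR of 2.0 per SD for referral, that it correlates 0.4 with pre-referral activation, and again that activation does not affect referral. Given literacy, the PAM variance is 1 − 0.4² = 0.84. Adjusting for a post-referral PAM changes the literacy log OR to ln 2 − 0.4d/0.84.

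- d = 0.2: 0.693 − 0.095 = 0.598, OR 1.82
- d = 0.5: 0.693 − 0.238 = 0.455, OR 1.58 (simulation 1.57)
- d = 0.8: 0.693 − 0.381 = 0.312, OR 1.37

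Adjusting for a pre-referral PAM left the OR at about 2.0 in the simulation.

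**4. Precision with 25 patients**

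Results gives 25 survivors enrolled but not how many referred nobody. Under an even split (12 and 13), which is the most favourable case, the standard error of the PAM difference in SD units is √(1/12 + 1/13) = 0.40. The 95% half-width is 1.96 × 0.40 = 0.78 SD. Any activation result is exploratory.

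**The case against.** The strongest reply is that the timing is simply not stated. The case for a post-referral PAM rests on one clause. The article goes on to describe the PAM as a general measure of self-management, and Quantitative Analysis lists it beside age, education and health literacy, as one would list an enrolment measure. This stands: a reader might infer that the model does adjust for its own consequence, but the document supports that only conditionally.

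Other strong readings also fail.

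- *Only one PAM is taken.* The article gives no number. The Abstract's list, "patient activation (cohort 1), perceived risk of LC, and generalized anxiety at baseline and at 28 days (cohort 2", attaches time points to the cohort 2 measures and says nothing about PAM frequency. A condensed article may leave the schedule to the full protocol.
- *The activation question has no analysis, or is answered in the wrong direction.* Association is symmetric: the derivation of exp(d) above shows that a mean difference and a logistic slope address the same null. Quantitative Analysis also compares referrers with non-referrers and provides t tests for continuous variables, which could cover PAM. It is fair to say only that no model with PAM as outcome is named. In the objective, *increased* may also mean a higher score and not a within-person change.
- *The study's stated hypothesis goes untested.* The hypothesis in the Introduction concerns willingness to refer and the behaviour of the referred population. Improved activation is a postulate of the Discussion.

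The effect sizes in the illustration are assumed and have no source in the document. The reply does not remove the contradiction between Data Collection and Quantitative Analysis, which is in the current text and holds under either timing.

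**Conclusion.** The point holds as a contradiction to be reconciled, with a conditional consequence. If the PAM is taken after referral, as Data Collection implies, its odds ratio in the referral model cannot be read as activation predicting referral, and other coefficients may be biased. Under the stated assumptions, a rise of 0.3 to 0.8 SD caused by referring gives an OR of 1.35 to 2.23 per SD with no true effect of activation. If it is taken before referral, the model stands on this point, the description does not, and that score cannot show that referring raises activation.

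The consequence is limited, since activation is not a listed outcome, but a directional claim in either sense would be unsupported as the text stands. The change should be made.

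**What to change.** 1. State in Data Collection, Cohort 1, when the PAM is given relative to the referral invitation and how many times, and align its description with Quantitative Analysis.
2. Keep PAM in the referral model, as predictor or covariate, only if it was recorded before that invitation.
3. For the activation part of the first objective, name an analysis with post-referral PAM as the outcome, by referral status or number of referrals, adjusted for a pre-referral PAM if one exists.
4. If there is only one PAM score, report a non-directional, exploratory cross-sectional association in the 25 enrolled patients and claim no increase.

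The cost is wording in the protocol or analysis plan; no new data are needed. The downside is a weaker claim about activation if no pre-referral score exists.
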